## Abstract

**Introduction:**

Paget’s disease of bone (PDB) is characterised by increased and disorganised bone remodelling affecting one or more skeletal sites. Complications include bone pain, deformity, deafness and pathological fractures. Mutations in sequestosome-1 (*SQSTM1*) are strongly associated with the development of PDB. Bisphosphonate therapy can improve bone pain in PDB, but there is no evidence that treatment alters the natural history of PDB or prevents complications. The Zoledronate in the Prevention of Paget’s disease trial (ZiPP) will determine if prophylactic therapy with the bisphosphonate zoledronic acid (ZA) can delay or prevent the development of PDB in people who carry *SQSTM1* mutations.

**Methods and analysis:**

People with a family history of PDB aged >30 years who test positive for *SQSTM1* mutations are eligible to take part. At the baseline visit, participants will be screened for the presence of bone lesions by radionuclide bone scan. Biochemical markers of bone turnover will be measured and questionnaires completed to assess pain, health-related quality of life (HRQoL), anxiety and depression. Participants will be randomised to receive a single intravenous infusion of 5 mg ZA or placebo and followed up annually for between 4 and 8 years at which point baseline assessments will be repeated. The primary endpoint will be new bone lesions assessed by radionuclide bone scan. Secondary endpoints will include changes in biochemical markers of bone turnover, pain, HRQoL, anxiety, depression and PDB-related skeletal events.

**Ethics and dissemination:**

The study was approved by the Fife and Forth Valley Research Ethics Committee on 22 December 2008 (08/S0501/84). Following completion of the trial, a manuscript will be submitted to a peer-reviewed journal. The results of this trial will inform clinical practice by determining if early intervention with ZA in presymptomatic individuals with *SQSTM1* mutations can prevent or slow the development of bone lesions with an adverse event profile that is acceptable.

**Trial registration number:**

ISRCTN11616770

Strengths and limitations of this studyThis is the first randomised placebo-controlled trial to test whether genetic testing coupled with targeted intervention with zoledronic acid can modify the development and progression of bone lesions secondary to Paget’s disease.The inclusion of individuals with sequestosome-1 mutations ensures that participants have a high risk of developing Paget’s disease and provides a suitable cohort in which to study the potential benefit of prophylactic treatment.The choice of zoledronic acid maximises the likelihood of preventing the development of bone lesions in this high-risk population.The randomised double-blind placebo-controlled design of the trial reduces the risk of selection and assessment bias.The study duration is unlikely to be sufficient to evaluate the effect of the intervention on complications of Paget’s disease such as bone pain, deformity and pathological fractures. Longer periods of follow-up of this cohort will be required.

## Background

Paget’s disease of bone (PDB) is characterised by areas of increased and disorganised bone turnover affecting one or more skeletal sites. Many affected individuals develop complications such as bone pain, deformity, deafness, pathological fracture and osteoarthritis. Genetic factors play an important role in PDB. Many genetic variants have been identified that predispose to PDB and related syndromes^1 2^ but mutations in sequestosome-1 (*SQSTM1*) are the most important predisposing factor, occurring in up to 50% of patients with a family history of PDB and up to 10% of people who are unaware of having a family history.^3–8^ Carriers of *SQSTM1* mutations have more severe disease with an earlier age at onset than patients who do not carry mutations.^9^ Cross-sectional studies indicate that the penetrance of PDB in *SQSTM1* mutation carriers is about 80% above the age of 70 years.^10^ However, there has been only one prospective study of disease evolution in mutation carriers. This study involved 10 families with *SQSTM1* mutations. Four out of 23 (17%) mutation carriers had developed the PDB disease by the age of 50 as assessed by radionuclide bone scanning, but the age at diagnosis was delayed compared with their parents’ age.^11^ Bisphosphonates are considered to be the treatment of choice for PDB, and within the bisphosphonates, zoledronic acid (ZA) is most likely to give a favourable response in terms of bone pain.^12^ ZA has a long duration of action in patients with established PDB with inhibitory effects on bone turnover that are superior to those of risedronate. 13 The main indication for bisphosphonate treatment in PDB is bone pain thought to be due to increased metabolic activity of the disease.^12 14^ Although bisphosphonates are highly effective at suppressing elevated bone turnover in PDB, there is no evidence that giving bisphosphonate treatment with the primary aim of suppressing elevated bone turnover is of clinical benefit.^14^ There is also no evidence that treatment can prevent complications of PDB such as fracture, bone deformity, deafness or secondary osteoarthritis.^14^
^15 16^ The Zoledronate in the Prevention of Paget’s disease (ZiPP) trial has been designed to determine if prophylactic treatment with ZA is effective at preventing the development or progression of bone lesions with the characteristic features of PDB in asymptomatic *SQSTM1* mutation carriers. The reason for choosing people with *SQSTM1* mutations is that these are relatively common in PDB and because carriers of *SQSTM1* mutations have a high risk of developing PDB with increasing age.

### Good clinical practice

The study will be carried out according to the principles of the International Conference on Harmonisation Tripartite Guideline for Good Clinical Practice and local guidance and regulations

### Consolidated standards of reporting trials

The results of the trial will be reported in accordance with the Consolidated Standards Of Reporting Trials statement.

### Aim

To improve clinical outcome in PDB by exploring whether genetic testing for *SQSTM1* mutations coupled with prophylactic treatment with ZA, can prevent or delay the development of bone lesions, prevent skeletal complications and favourably modify pain and quality of life in those genetically at risk because of a positive family history.

### Objectives

The study objectives are summarised in box 1 and described in more detail below:

Box 1Outcome measures for the Zoledronate in the Prevention of Paget’s disease trialPrimaryThe total number of subjects who develop new bone lesions on radionuclide bone scans with the characteristics of Paget’s disease of bone (PDB) between the baseline visit and the final follow-up visit.SecondaryThe number of new bone lesions on radionuclide bone scan.Change in activity of existing bone lesions that were present at the baseline assessed by semiquantitative analysis of radionuclide bone scans.^28^
The development of PDB-related skeletal events defined as any one of the following:Development of new bone lesions thought to be due to PDB on imaging.Development of complications thought to be due to the development or progression of PDB including pathological fractures, bone deformity, deafness, joint replacement surgery or other orthopaedic procedures.Administration of treatment for PDB with an antiresorptive drug because of the development of signs or symptoms thought to be due to PDB such as pain localised to an affected site or neurological symptoms.The development of increased bone turnover as assessed by measurement of biochemical markers of bone resorption and bone formation.Quality of life, anxiety and depression assessed by the Short Form (36) Health Survey, Brief Pain Inventory (BPI) and Hospital Anxiety and Depression Questionnaire.Location, presence and severity of pain assessed by the BPI manikin and pain questionnaire.

#### Primary objective:

To quantify the number of subjects in each treatment group who develop new bone lesions with the characteristics of PDB as assessed by radionuclide bone scan. The presence and location of lesions will be assessed by imaging experts blinded to treatment allocation. A new bone lesion will be defined as evidence of involvement of a new bone or part of a previously affected bone at the end-of-study visit which was not thought to be involved at the baseline visit.

##### Secondary objectives:

To quantify the number of new bone lesions and change in activity of existing bone lesions present at baseline; to evaluate the effects of treatment on skeletal events related to PDB; to evaluate the effects of treatment on biochemical markers of bone resorption and bone formation and to evaluate the effects of treatment on health-related quality of life (HRQoL), anxiety and depression and the presence, localisation and severity of pain.

### Outcome measures

The schedule of assessments and outcome measures, which will be collected during the study, are summarised in table 1 and are discussed individually in more detail below.

**Table 1 T1:** Summary of assessments and outcome measures for the ZiPP trial

	Screening	Baseline visit	+1 week	Annual review	End of study
Medical history		✓		✓	✓
Current medication		✓		✓	✓
Physical examination		✓			
Height, weight, blood pressure		✓			✓
Routine biochemistry*	✓	✓		✓	✓
Haematology†		✓			✓
Blood for biomarkers‡		✓		✓
Urine for biomarkers§		✓			✓
SQSTM1 genotyping	✓				
25(OH) vitamin D	✓				
Pregnancy test¶ (in women of childbearing potential)		✓			
Radionuclide bone scan		✓			✓
Radiographs or other imaging**		✓			✓
Infusion		✓			
Telephone Questionnaire			✓		
Food Frequency Questionnaire		✓			
SF-36, HADS and BPI questionnaires		✓		✓	✓
PDB-related skeletal events					✓

*Calcium, albumin/total protein, alkaline phosphatase, liver function (AST, ALT, GGT, bilirubin), urea and electrolytes and creatinine.

†Full blood count.

‡Blood samples for measurement of bone-specific alkaline phosphatase, PINP, CTX-I and other specialised markers of bone metabolism.

§Second-voided morning urine to be taken and stored for measurement of N-telopeptide collagen cross links, deoxypyridinoline/creatinine ratio and other specialised markers of bone metabolism.

¶A negative pregnancy test must be obtained on the day of, or the day before, infusion of the study drug. The preferred method of is serum beta-hCG, but a urine beta-hCG is acceptable for centres that are unable to obtain a serum beta-hCG.

**To be taken of relevant areas in subjects suspected to have PDB-like bone lesions on bone scan.

ALT, Alanine aminotransferase; AST, Aspartate aminotransferase; BPI, Brief Pain Inventory; CTX-I, C-terminal telopeptide of type I collagen; GGT, Gamma glutamyl transferase; HADS, Hospital Anxiety and Depression Questionnaire; hCG, Human chorionic gonadotrophin; PDB, Paget’s disease of bone; PINP, N-terminal propeptide of type I procollagen; SF-36, Short Form (36) Health Survey; *SQSTM1*, sequestosome-1; ZiPP, Zoledronic acid in the Prevention of Paget’s disease.

#### Bone lesions

These will be assessed by Tc^99^ radionuclide bone scan, which is recognised to be the most sensitive imaging technique for identifying bone lesions in PDB.^14^
^17^ Participants thought to have PDB-like bone lesions on scan may have further imaging performed by X-ray, CT scan or MRI scan if the local investigator considers it clinically indicated. Anonymised bone scan and X-ray images will be uploaded on to the study database for review. All scans will be reviewed by an imaging expert blinded to treatment allocation. A proportion of images will be reviewed by a second imaging expert, also blinded to treatment allocation, to evaluate concordance between the observers. The images selected will include all of those considered by the primary imaging expert to represent PDB-like lesions. In the event that the experts disagree on a specific image, a third imaging expert (also blinded to treatment allocation) will be asked to adjudicate.

#### Clinical assessments

Participants will undergo a physical examination at the baseline visit including blood pressure and pulse. Participants will be evaluated clinically at the end-of-trial visit for any symptoms or signs of skeletal events thought to be related to PDB.

#### Biochemical markers

Measurements of serum creatinine, urea and electrolytes, serum total alkaline phosphatase (ALP), serum calcium, albumin and liver function tests which will consist of aspartate aminotransferase (AST) alanine aminotransferase (ALT), gamma glutamyl transferase (GGT) and bilirubin along with a full blood count will be performed using standard techniques at the local laboratories in participating centres. Estimated glomerular filtration rate (GFR) will be calculated from serum creatinine, gender and weight by the Cockcroft-Gault equation. 18 Specialised biochemical markers of bone turnover will be measured centrally at the University of East Anglia. These will include urine N-telopeptide collagen cross links (NTX) corrected for urinary creatinine; C-terminal telopeptide of type I collagen (CTX-I), bone-specific alkaline phosphatase (BSAP) and the N-terminal propeptide of type I procollagen (PINP). These measurements will be made on fasting samples collected between 09:00 and 12:00 hours as previous studies have shown that markers of bone resorption have a circadian rhythm and are influenced by food intake.^19^ The urine samples will be second-voided ‘spot’ samples collected after an overnight fast. The preferred markers of bone resorption are urinary NTX and serum CTX-I. These have been found to be elevated in patients with PDB in case–control studies 14 and to correlate with the extent of bone lesions as determined by scintigraphy in PDB.^20^ The preferred markers of bone formation will be PINP and BSAP since both have been shown to be superior to total ALP at detecting PDB in case–control studies.^14^ Additional biomarkers of bone metabolism may also be assessed if new information indicates that these may be of interest as the study progresses. The serum, plasma and urine samples will be aliquoted and stored locally at −80°C and shipped on dry ice to the central laboratory.

#### Health-related quality of life

HRQoL will be assessed by completion of the Short Form (36) Health Survey (SF-36) questionnaire^21^ at baseline, annual visits and the end-of-study visit. The SF-36 is a widely used, validated questionnaire^21^ previously used to assess quality of life in patients with established PDB.^15 16^

#### Pain

The presence and location of pain will be assessed by completion of the Brief Pain Inventory (BPI)^22^ at baseline, annual visits and the end-of-study visit. The BPI was originally developed to evaluate the location and severity of pain in patients with malignant disease but has since been validated in people with chronic non-malignant pain.^23^ In addition to completing BPI, participants will also be asked if they have experienced any pain and bone pain

#### Anxiety and depression

Anxiety and depression will be assessed by the Hospital Anxiety and Depression Questionnaire (HADS).^24^ This questionnaire was chosen since it is quick and simple to administer and has it has been extensively validated in many different countries and settings.^25^

#### Paget’s disease-related skeletal events

Participants will be evaluated clinically at the end of study for the presence of Paget’s disease-related skeletal events (PDRSE). These will include pathological fractures, bone deformity, deafness due to skull involvement, and joint replacement surgery or other surgical procedures that are a carried out because of PDB. Administration of an antiresorptive drug during the study because of signs or symptoms that are thought to be due to PDB will be considered as a PDRSE as will the development of new bone lesions on bone scan. All events will be combined for each treatment group to give a total score.

#### Genetic testing

Genetic testing will be conducted to determine eligibility by Sanger sequencing of exons 7 and 8 of *SQSTM1* and the intron–exon boundaries using DNA extracted from a venous blood sample according to standard techniques.^9^

### Sample size

The sample size was chosen assuming that 15% of patients in the placebo group and 1.5% of patients in the active (ZA) treatment group will develop new PDB-like bone lesions during follow-up. This was based on the observation that ZA has been reported to normalise biochemical markers of bone turnover for up to 6.5 years in 90% of patients with established PDB.^26^ With this assumption, 85 subjects in each group would provide 89% power to detect a treatment effect of this magnitude at an alpha of 0.05. Since it is possible that more than one affected subject per family could be enrolled, the sample size was inflated to account for relatedness of individuals. This was done by calculating the mean squared alkaline phosphatase values in patients within families who carried the same mutation (271.3) and the mean squared alkaline phosphatase values between families (619.7) and combining this with the estimated average number of two subjects per family who may be enrolled in the study. This resulted in a design effect factor of 1.39, inflating the required sample size to 118 per group. In addition to this, the sample size was further inflated to account for a 10% rate of participants lost to follow-up resulting in a total sample size of 130 subjects per group or 260 subjects in total. The actual number of subjects randomised to the interventional study by the time recruitment had closed in April 2015 was 222 and to the observational study was 135. The decision to stop recruitment was based on funding, and justified by recalculating the design factor based on the actual number of subjects per family that had been enrolled into the study (1.5 on average). The design factor was recalculated to be 1.26.

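### At the recalculated design factor of 1.26, the plan's own 10% loss allowance still requires 236 to 238 participants, so the recalculation does not by itself justify stopping at 222

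*Protocol article*

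**What the plan says.** All of this is in the Sample size section of the protocol article. The assumed event rates are that "15% of patients in the placebo group and 1.5% of patients in the active (ZA) treatment group will develop new PDB-like bone lesions", and "85 subjects in each group would provide 89% power to detect a treatment effect of this magnitude at an alpha of 0.05". For relatedness within families, the section takes mean squares of alkaline phosphatase of 271.3 within and 619.7 between families, with "the estimated average number of two subjects per family who may be enrolled in the study". It obtains a design effect of 1.39 and 118 per group. Then "the sample size was further inflated to account for a 10% rate of participants lost to follow-up", which gives 130 per group, 260 in total.

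The section goes on to report that 222 were randomised by the close of recruitment in April 2015. It names funding as the basis for stopping and says that the decision was "justified by recalculating the design factor based on the actual number of subjects per family that had been enrolled into the study (1.5 on average"). It ends: "The design factor was recalculated to be 1.26". It states no revised target, loss rate or power at that factor.

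**The concern.** The section builds its target in three steps: a base number, a design factor, and a loss allowance. The justification for 222 changes the second step and does not mention the third. The 10% allowance is never withdrawn, and follow-up runs for 4 to 8 years (Abstract, Methods and analysis). If 1.26 is carried through the whole chain, the target falls below 260 but stays above 222.

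At stake is how the achieved sample size is described. The only power figure in the section is 89%, tied to 85 per group before any inflation, and the text offers a statistical justification for 222 without saying what power 222 gives.

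**Working it through.** **Inputs, all from the Sample size section.** Event rates 15% and 1.5%; 85 per group; alpha 0.05; mean squares 619.7 (between) and 271.3 (within); two per family planned, 1.5 observed; 10% loss; 222 randomised. Two assumptions are added: a two-sided test, and equal allocation (111 per group).

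**1. The plan's own chain.**
- Power at 85 per group, pooled two-proportion formula: Φ[(0.135 − 1.96 × √(2 × 0.0825 × 0.9175/85)) / √((0.15 × 0.85 + 0.015 × 0.985)/85)] = 89.9%. Fisher's exact test also gives 89.9%. The plan states 89%.
- Intraclass correlation: (619.7 − 271.3)/(619.7 + 271.3) = 348.4/891.0 = 0.391.
- Design effect at two per family: 1 + (2 − 1) × 0.391 = 1.391, stated as 1.39.
- 85 × 1.39 = 118.15, stated as 118. Then 118 × 1.1 = 129.8, stated as 130.

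The original chain reproduces. It also shows that the plan applies its loss allowance by multiplying by 1.1.

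**2. The factor of 1.26.** Family sizes averaging 1.5 must be unequal. The design effect for unequal sizes replaces the mean size by Σm²/Σm. For an even mix of ones and twos this is (0.5 × 1 + 0.5 × 4)/1.5 = 1.667, and 1 + 0.667 × 0.391 = 1.2607. This rounds to the stated 1.26. The even mix is an assumption. It is the most favourable case for whole-number sizes averaging exactly 1.5; for example, 60%, 30% and 10% of families with one, two and three members would give 1.31.

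**3. The same chain at 1.26.**
- 85 × 1.26 = 107.1 per group, 214.2 in total.
- With 10% loss, by the plan's convention: 107.1 × 1.1 = 117.8, so 118 per group, 236 in total.
- With 10% loss, by division: 107.1/0.9 = 119.0, so 119 per group, 238 in total.
- Shortfall: 236 − 222 = 14, or 238 − 222 = 16.
- Loss that 222 can absorb: 1 − 214.2/222 = 3.5%.

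**4. Power for 222 at 1.26.**

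| Loss | Evaluable per arm | Effective per arm | Power (pooled) |
|---|---|---|---|
| 0% | 111.0 | 88.1 | 90.9% |
| 3.5% | 107.1 | 85.0 | 89.9% |
| 5% | 105.5 | 83.7 | 89.5% |
| 10% | 99.9 | 79.3 | 87.8% |

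At 10% loss the effective number is 79.3 against 85, a deficit of 5.7 or about 7%. By Fisher's exact test, power is 86.7% at 79 per arm against 89.9% at 85, so the gap is somewhat larger there but still modest.

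**The case against.** The strongest reply is that the article claims little. It names funding as the reason for stopping, discloses 222 against the planned 260, and never says that 222 meets the target or keeps 89% power. The lower factor does cut the requirement, from 260 to about 236, so the recalculation is a partial justification. The power cost is small, and a journal article may leave revised power and the family-size distribution to the full protocol.

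Most of this stands. It is why the point is minor, and why the missing distribution is not itself a finding. It does not remove the point: the article chose to print a statistical justification, and that figure, put through the section's own steps, gives a target above 222.

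A reader might also infer that 1.26 is an arithmetic error, because 1 + 0.5 × 0.391 = 1.20, or 1.23 if the intraclass correlation is recomputed with 1.5 per family. The document does not support that. Those values come from a formula for equal family sizes, which cannot apply literally to a mean of 1.5, whereas step 2 reaches 1.26 from the plan's own inputs.

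**Conclusion.** The point holds as a minor one. At 1.26 with the section's 10% loss allowance, 222 is 14 to 16 participants below the implied 236 to 238. Power is about 88% by the pooled formula, 1 to 2 points below the 89% stated or 89.9% computed for 85 per arm. The result rests on equal allocation, a two-sided test, the plan's event rates, its method for the design effect, and the 10% allowance still applying. If loss turned out at 3.5% or less, 222 would suffice.

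Two stronger readings should be resisted. The trial is not badly underpowered on its own assumptions. Nor does the article assert that 222 preserves the planned power; a reader may infer it from the word 'justified' and the lone 89%, but it is not stated.

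**What to change.** Keep 1.26 and do not replace it with 1.20 or 1.23. After the sentence that gives it, add text along these lines: *At a design factor of 1.26, the original calculation with a 10% allowance for loss implies 236 to 238 participants. The 222 randomised, with 10% loss, give about 88% power under the original event-rate assumptions. The recalculation reduces the shortfall against the original target but does not by itself justify 222; recruitment stopped for funding reasons.*

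The shortfall falls from 38 (260 − 222) to 14 to 16. If the authors now expect a loss other than 10%, they should state that rate and give the power for it.

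The cost is a few lines of text and a slightly less favourable stated power. Design, endpoint and analysis are unaffected.
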